### Recruitment/inclusion and exclusion criteria for participants

Practices will be recruited primarily through SaxoForN [35, 36], which is a German practice-based research network (PBRN [37]) that is being established in Saxony and Hesse and GP practices associated with the study teams’ institutes. Participation is open to general and internal medicine practices that provide full care (incl. home visits) and did not participate in our first qualitative study.

GP practice teams (GP and HCA) will receive an online educational training followed by a telephone call (training 1) to prepare them for patient recruitment. The GP practice teams will then use a standardized procedure to recruit patients over a period of 3–4 weeks. The inclusion criteria are as follows: aged ≥ 65 years, two or more chronic diseases, five or more chronic medications, ≥ one hospitalization in the past 12 months, and sufficient knowledge of German (reading and language comprehension). Patients that are unable to provide consent, live in a nursing home, suffer from diagnosed severe mental disorders (ICD-10 F diagnoses), or that participated in our first qualitative study will be excluded.

Each GP practice will filter as many of these criteria as possible using their practice management system and will create a list of patients that fulfill them. The filtered criteria and number of patients will be documented. Letters will then be sent to patients by post to invite them to participate. Only patients that have a regular appointment in the practice within the specified period of 4 weeks will be invited. In view of the future definitive trial, two slightly different approaches will be used in Hesse and Saxony with the aim to compare and to examine their feasibility. In Hesse, patients fulfilling the study criteria will be invited in the order of their appointments in the practice, starting with the first 20 patients. In Saxony, after filtering the criteria, the study team will then assign an individual random letter taken from the alphabet to the practice. The GP practice will check the criteria that have not been filtered yet, starting with the first patient whose name begins with that letter. This process will be repeated for every fifth patient on the entire list until 20 patients have been identified.

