### Allocation and blinding

To avoid contamination of the IG and CG, the level of randomization will be the GP practice (cluster randomization) stratified based on study site. Upon inclusion, each GP practice will be allocated a consecutive number by the study team (pseudonym). In preparation for block randomization, an online tool [38] will be used to generate a random list of the two study arms in blocks of 6 and 4 for each study region. The pseudonym of the practices will be entered into the randomization list in the order in which participating patients from a specific GP practice complete the baseline surveys (t0). The GP practice will thus be randomly assigned to one of the study arms. The randomization process will be administered confidentially by two researchers from one of the study teams’ institutes that are not involved in the study.

All participants will be blinded. After block randomization, GP practices will receive study materials and training according to their assigned study arm (training part 2, digital). After completion and evaluation of the study, all participants will receive a booklet containing an overview of the methodology and main results of the study. The statistical analysis will be performed by blinded staff at Ruhr University Bochum (cooperation partner).

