### Feasibility of the outcomes measuring for the future definitive trial

In the pilot trial, we are testing the *primary endpoint* for the future definitive trial, which will be the combined endpoint of health-related patient outcomes (hospitalization, falls, and mortality), as shown in Table 1. *Secondary endpoints* for the future definitive trial will include improvement in information on medications (SIMS-D questionnaire [44]), a reduction in symptoms and/or side effects of the medication (pro-CTCAE questionnaire [45, 46] adjusted), an improvement in health literacy (HLQ-G questionnaire [47]), and improving the medication and treatment-related information: comparing the available information regarding the care situation between GP and patient (FIMA [48, 49]).

**Table 1 Tab1:** Description of the combined endpoint for the future definitive trial

**Endpoint (quantity)**	**Patients**		**GP Practice**	
	**Data**	**Instrument**	**Data**	**Instrument**
Hospitalization	X	Single question regarding hospitalization including frequency and length of stay from FIMA [48, 49]	X	Single question regarding hospitalization including frequency and length of stay from FIMA [48, 49]
Falls	X	Standardized documentation (self-report)		
Mortality			X	Standardized documentation

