#### GP practice

At *baseline*, information on the practice (such as practice size, practice type, and location), as well as sociodemographic information for the GPs and HCAs (such as sex, age, professional experience), will be collected using a self-administered questionnaire. Furthermore, the diseases of each included patient will be collected by 14 disease groups (based on the “Cumulative Illness Rating Scale” (CIRS) [50]).

At both *baseline* and *follow-up*, the standardized and validated FIMA questionnaire [48, 49] will be collected for each included patient. The FIMA (German acronym for “Questionnaire for Health-Related Resource Use in an Elderly Population” — Fragebogen zur Erhebung von Gesundheitsleistungen im Alter) “collects the health-related resource use within the older population groups” [48]. The questionnaire will be slightly modified, so that the questions are suitable for use in GP practices and reflect the patient data that is available to them. As an alternative to entering medications in the FIMA, practices may also send a copy of an existing medication plan to the study team. Mortality will be surveyed during the study (standardized documentation).

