#### Patients

At *baseline*, a self-administered questionnaire will be used to collect data on sociodemographic characteristics (such as sex, age, and living situation), as well as knowledge and use of an electronic patient file (ePA in Germany). At both *baseline* (t0) and *follow-up* (t1), a medication plan will be required, along with information on the number of falls within the last 3 months (based on the WHO definition [51]) and on symptoms and/or side effects of the medication (selection of the German patient-reported outcomes version of the Common Terminology Criteria for Adverse Events (NCI PRO-CTCAE™ Items-GERMAN [45, 46]). Furthermore, validated and standardized questionnaires will be used:FIMA: Fragebogen zur Inanspruchnahme medizinischer und nicht-medizinischer Versorgungsleistungen im Alter (Questionnaire for Health-Related Resource Use in an Elderly Population) [48, 49]HLQ-G: Health Literacy Questionnaire — German [47]SIMS-D: Satisfaction with Information about Medicines Scale, German version [44]

Patient enrolment is scheduled to start in March and will be completed in May 2022. Data collection is expected to end in November 2022. The participant timeline is shown in Table 2.

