### Analysis

Wherever appropriate, interview transcripts will undergo content analysis based on Mayring [53] and through the use of MAXQDA. Quantitative and qualitative data will be analyzed descriptively with focus on the following:
*Feasibility*
The recruitment and randomization process will be presented descriptively. Adherence to the planned way of realization will be assessed. Furthermore, a descriptive analysis will be performed to compare the two study groups.Content-oriented description of participants’ comprehension of and adherence to the intended implementation of the intervention’s components, their expectations, and experiences throughout the study periodAnalysis for the maintenance of blinding will be done at patient and cluster level. At a patient level, mixed logistic regression analysis will be performed with dependent variable “patient correctly guess treatment group” and independent variable treatment group and a random cluster effect. Similar, at cluster level, logistic regression analysis will be performed with outcome “GP correctly guess treatment group” and independent variable treatment group. If the random cluster effect in the analysis at patient level is large, we will further explore the association between GPs guess and patients guess through logistic regression.
*Exploration of possible effects*: One possible effect of the intervention is an improvement in health literacy, as assessed using the HLQ-G. A linear mixed model that employs intervention group, HLQ-G at baseline, age, sex, and cluster as the independent variables will be used to evaluate the effects.

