*Analysis of the combined endpoint*: A mixed logistic regression model will be used to analyze the planned combined endpoint, which is a combination of death, hospitalization, and falls (dichotomous), similar to the analysis planned in the main trial. In addition to study group, age and sex will be included as fixed effects, with the cluster added as a random effect. If a significant proportion of patients (> 10%) experience multiple events for falls and hospitalizations, we will perform additional separate analyses for these outcomes that uses a mixed negative binomial model. The sample size calculation for the future definitive trial will be based on the results of these models. Sensitivity analyses will be performed for per-protocol group.Agreement and differences in FIMA results between patients and GPs will be analyzed using agreement parameters such as Kappa statistics.

The resulting assessment of the clinical relevance of the outcomes and the findings of the process evaluation will be used in planning the future definitive trial. Statistical analyses of intervention effects will be performed as part of the future definitive trial. Exploratory analyses will be performed according to the intention to treat principle.

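### Neither effect model includes study site, the randomisation stratum, and the composite model leaves out baseline falls and admissions already collected; if the sites differ, the ICC passed to the definitive trial is overstated

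*Protocol article*

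**What the plan says.** Under Allocation and blinding, the protocol article states that "the level of randomization will be the GP practice (cluster randomization) stratified based on study site", using a "random list of the two study arms in blocks of 6 and 4 for each study region". With 10 practices per site (Sample size), one block of each length gives five practices per arm within each site.

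Under Recruitment, the sites select patients differently. Hesse invites patients in the order of their appointments. Saxony starts from a random letter of the alphabet and takes every fifth patient on the list. The stated purpose is to compare the two approaches.

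The Analysis section writes out the terms of both models. For health literacy it is "A linear mixed model that employs intervention group, HLQ-G at baseline, age, sex, and cluster as the independent variables". For the combined endpoint, a mixed logistic model: "In addition to study group, age and sex will be included as fixed effects, with the cluster added as a random effect". Site is in neither. The same section bases the sample size of the definitive trial on the results of the composite model and the optional negative binomial models.

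Baseline values of two of the three composite components are collected. Patients give "information on the number of falls within the last 3 months" at t0 and t1. At both times practices also report on each patient: "the standardized and validated FIMA questionnaire [48, 49] will be collected for each included patient". Table 1 describes the admissions item as "Single question regarding hospitalization including frequency and length of stay from FIMA". Eligibility requires "≥ one hospitalization in the past 12 months".

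**The concern.** A model for a stratified design should normally contain the stratum. Here the strata differ by region and also, deliberately, by the way patients are sampled. Selection by order of appointment could favour frequent attenders, so a difference in event risk between sites is plausible. With site left out, the model has nowhere to put that difference except the practice random effect. The practice variance is a main output of this pilot, because the definitive sample size rests on the composite model.

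The second issue is an inconsistency. The HLQ-G model adjusts for the baseline value of its outcome. The composite model does not, although prior falls and prior admissions are recorded at t0. With about 10 practices per arm, chance imbalance in prior events can be appreciable and would go uncorrected.

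**Working it through.** **Inputs from the article.** 20 practices × 10 patients = 200, which matches the stated total. There are 10 practices per site, expected 5:5 by arm within site. The article states no ICC, event rate or site difference, so those below are assumptions.

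**Site: effect on the ICC and standard error.** Assume a within-site ICC of 0.03 on the latent logistic scale and an event rate of 40%.

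- Practice variance: 0.03/0.97 × π²/3 = 0.102.
- Omitting site adds (ln OR / 2)².
- Apparent ICC = s²/(s² + 3.29), where s² is the total practice variance.
- Design effect = 1 + 9 × ICC for 10 patients per practice.
- Model SE of the log odds ratio = √[2 × (s² + 1/(10 × 0.24))/10].

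| Site OR | Added variance | s² | Apparent ICC | Design effect | Model SE |
|---|---|---|---|---|---|
| 1.0 | 0 | 0.102 | 0.030 | 1.27 | 0.322 |
| 1.65 | 0.063 | 0.164 | 0.048 | 1.43 | 0.341 (+6%) |
| 2.0 | 0.120 | 0.222 | 0.063 | 1.57 | 0.357 (+11%) |

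At OR 1.65 a definitive trial with the same cluster size would need about 12% more patients (1.428/1.270 = 1.125).

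**Sensitivity to the assumed ICC.** The next figures multiply the added variance by 20/19 for the finite number of practices. The patient numbers illustrate a comparison of 40% with 30% at two-sided 5% and 80% power.

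| True ICC | Site OR | Apparent ICC | Patients per arm, true → apparent |
|---|---|---|---|
| 0.01 | 1.25 | 0.014 | 389 → 401 |
| 0.01 | 1.5 | 0.023 | 389 → 429 |
| 0.01 | 2.0 | 0.046 | 389 → 505 |
| 0.05 | 1.25 | 0.054 | 517 → 528 |
| 0.05 | 1.5 | 0.062 | 517 → 554 |
| 0.05 | 2.0 | 0.084 | 517 → 624 |

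**Simulated check.** Random-intercept logistic models were fitted by maximum likelihood.

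- *Mechanism.* With 200 practices, true ICC 0.05, site OR 1.5 and the baseline event in the model, the mean ICC was 0.062 without site and 0.049 with it. This agrees with the formula.
- *Effect estimate.* At pilot size with site OR 1.5, the mean log odds ratio was −0.491 without site and −0.494 with it, and its SD was 0.373 and 0.375. The balanced stratified allocation already removes site from the arm contrast, so only the model's reported SE carries the excess.

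**Baseline events: effect on the ICC and power.** Pilot size, baseline-event OR 3, true ICC 0.05, no site effect:

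| | Baseline event omitted | Included |
|---|---|---|
| Mean log OR | −0.513 | −0.544 |
| SD of log OR | 0.350 | 0.361 |
| Effect/SD | 1.469 | 1.507 |
| Mean ICC | 0.040 | 0.046 |

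Including the baseline event raises the estimated ICC and the SD of the log odds ratio, but moves the effect further from zero. The net gain is 1.507/1.469 = 1.026. Across the pilot scenarios it was about 1–3%, and with 200 practices 0–7%.

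**Baseline events: chance imbalance.** Assume 25% baseline fallers and a design effect of 1.27. The SD of the between-arm difference is √[2 × 0.25 × 0.75/(100/1.27)] = 0.069, so the 95% range is about ±13.5 percentage points. If prior falling has an OR of 3 for the outcome, a 13.5-point imbalance shifts the log odds ratio by 0.135 × ln 3 = 0.148, an OR of 1.16. A one-SD imbalance gives about 1.08.

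**The case against.** The strongest reply is that this is an exploratory pilot with no sample size calculation. The article defers statistical analysis of intervention effects to the definitive trial. No site rates are given, and it calls the two selection procedures only slightly different. If the sites do not differ, nothing is inflated. Where they do, the larger model SE is conservative. All of this stands and limits the severity.

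A second reply is that adding site can worsen the ICC estimate. With 20 practices, maximum likelihood with site in the model underestimates it. At a true ICC of 0.03, simulated means without and with site were 0.029 and 0.023 at site OR 1.0, 0.030 and 0.023 at 1.25, and 0.044 and 0.025 at 1.65. For small site effects the published model is therefore closer to the truth, and the error of the adjusted model runs towards an undersized definitive trial. The sampling SD of the ICC is about 0.04–0.05, so a shift of 0.018 is less than half of one SD. This also stands. It argues for reporting both versions with their uncertainty and a small-sample estimate. It does not argue for leaving the stratum out altogether.

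Third, chance imbalance is not bias. A log odds ratio shift of 0.148 is less than half of an SE of about 0.32–0.35, and the unadjusted interval already allows for it. That is correct; the case for adjustment is consistency with the HLQ-G model and a modest gain.

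A reader might infer that leaving out the baseline events also inflates the ICC, or that leaving out site makes the estimate less precise. The simulations support neither.

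**Conclusion.** The point holds in a limited form. Both models omit the factor on which randomisation is stratified. The composite model also omits baseline counts that are collected, while the HLQ-G model adjusts for its baseline. Both covariate lists are written out, so these are stated choices.

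Overstatement of the ICC and of the model SE comes only from omitting site, and only if event risk differs between sites. Under a within-site ICC of 0.03 and 40% events it ranges from nothing at site OR 1.0 to an ICC of about 0.063 and an SE 11% too large at OR 2.0. The documents cannot say where in that range the trial will fall. The size is worked out for the composite only; for HLQ-G the same mechanism applies but is not quantified. The stronger reading, that the ICC is certainly inflated, is therefore not supported.

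Omitting the baseline events costs a little power and leaves chance imbalance uncorrected. Severity is moderate at most. The reason to act is that the definitive sample size depends on the composite model.

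**What to change.** - Add study site (Hesse/Saxony) as a fixed effect to the HLQ-G and composite models.
- Add the t0 number of falls and the t0 number of hospitalisations to the composite model and to the negative binomial models. Use a count for hospitalisations: a yes/no term over 12 months would be constant under the inclusion criterion.
- Report the ICC with and without site, each with a confidence interval, and use a small-sample (REML-type) estimate where available. State which value goes into the definitive sample size, and do not rely on the maximum likelihood value with site alone.

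The cost is one to three extra terms from data already collected, and one of about 18 between-practice degrees of freedom for site. No additional data collection is needed.

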## Discussion

Our study will address the need to ensure high-quality information is available at the interface between inpatient and outpatient care and available to the patients themselves. Literature shows that insufficient information is associated with preventable adverse health events [1, 4, 8, 9, 13–15]. Our intervention therefore aims to empower patients and GP practices by improving information on patients’ health conditions. Furthermore, the study results will provide valuable feedback to further develop the German electronic patient record ePA: focusing (a) which health-related data are the most important, (b) who could provide respectively which sources could be used for this, (c) aspects of data economy, and (d) user acceptance.

Other studies have already shown the importance of piloting large-scale intervention studies in advance [18]. By using a pilot and feasibility cluster-randomized controlled trial, we will gain insights and gather experiences that will help plan and implement the future definitive trial. This will include information on the actual use of the intervention documents and feedback from the GP practice teams on whether parts of the intervention (e.g., “GP practice Checklist”) should be digitalized further in the future definitive trial. Furthermore, we will gain insight in feasibility and on effectiveness of the outcome measures.

Even if the intervention can be integrated well into daily routines, it may be time-consuming. However, we assume that the intervention will improve informational continuity of care and possibly simplify the existing coordination tasks of GP practices. In the long term, this should save time and speed up the exchange of information with other healthcare providers and patients.

Results will be disseminated via publication in open-access peer-reviewed scientific journals and at congresses and conferences. Furthermore, a project report on the results will be presented to the funder, and a booklet containing an overview of the study will be developed in plain language for participants and the general public. There are no restrictions on publication.

### Strengths and limitations

The intervention was developed using a participatory approach, i.e., with the involvement of stakeholders that are directly affected by or confronted with the challenges and impacts of the availability of health information in everyday life and routine care [28]. The intervention should therefore be easy to integrate into daily practice routines and procedures. The relevant participants/addressees in this pilot study will consist of the same stakeholder groups (healthcare providers and patients). In GP practices, study tasks will be shared among teams of GPs and HCAs, with both professions involved and responsible for carrying out important tasks. The results will show exactly how these tasks are divided up within the teams and whether and how the implementation can be integrated into daily practice routines.

Participating GP practices will receive study information step-by-step to minimize selection bias in patient recruitment. The participants and data analysts will all be blinded.

The study may be negatively affected by difficulties recruiting participants as a result of the COVID-19-related burden on GP practices of the vaccination campaign, discussions about compulsory vaccinations, potential practice closures, increased testing volume (PCR tests — polymerase chain reaction test) and sick leave among personal. However, the timetable set by the funder cannot be postponed any further, especially as it is not possible to predict when and how the situation may change in the future.

## Conclusion

The present study addresses an important topic in everyday care and aims to test the feasibility of a complex intervention aimed at improving information continuity at the interface between inpatient and outpatient care with the participation of patients. It will further investigate the feasibility of the study design. The results will be used to plan the future definitive trial, which will examine both the efficacy and cost-effectiveness of the intervention.

